**2.4 Endoscopic mucosal imaging and ultrasound**

- During upper endoscopy for scheduled biopsies (see 2.3 above), pictures of the transplant duodenal mucosa will be taken.

- The mucosal images will be rated regarding rubor, edemea villous

atrophy etc. and compared to biopsy rejection scores.

- Endoscopic ultrasound (EUS) will be used when taking biopsies of the pancreas. EUS images will be sampled and stored, for comparative analysis.

- The EUS analysis will mainly involve circulatory parameters.

**2.5 Donor and recipient baseline characteristics**

- We will investigate relationships between the below mentioned donor/recipient characteristics and graft survival/surgical complications/non-surgical complications.
- Donor age
- Donor gender
- Donor BMI
- Recipient age
- Recipient gender
- Recipient BMI
- Recipient PRA (Panel Reactive Antibody) status
- Recipient comorbidity status; particularly cardiovascular status

**2.6 Non-immunological rejection markers**

- The following analyses will be performed and correlated to rejection, functional parameters (glucose levels/need for insulin (P) and creatinine (K)) and graft survival.

– By daily blood samples during the first 10 days, thereafter 3 times a week until week 10. Plasma from these samples will be frozen – to allow for subsequent analyses. .

- - Amylase (pancreas specific amylase)
  - Lipase
  - CRP
  - Amylase/Lipase/CRP combined parameter
  - C-peptide and C-peptide/Glucose/Creatinine-ratio (C-peptide : Glucose x Creatinine)
  - Pancreas Auto-Antibodies

In addition, amylase in drainage fluid will be measured daily, until the drains are removed (usually at day 4-8 post-Tx).

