**5 NUMBER OF PATIENTS**

60-80 patients will be enrolled in the study and all will receive the standard quadruple immunosuppressive regime with reduced CS dosing compared with previous cohorts (according to newly changed routine protocol).

####

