2. The maximally realistic number of PTx patients to be included in Oslo during a reasonable time frame (2-3 years) will be 60-80.
3. Thus, our intentions with regard to statistical Power have to be more modest. The above figures (lower table) do however show that a doubled rejection rate in the trial arm can be detected at 60% Power with 27 x 2 = 54 patients.
4. The prospects/visions of this study consist of a lot more than detecting significant changes in rejection/complication rates. Please, cfr. paragraphs 2.2 – 2.6 of this protocol. The simultaneous biopsy strategy (D- + P- + K-biopsies) is unique. And the ‘molecular biology’ analyses of these simultaneous biopsies and blood samples have the potential to provide new insights. Furthermore, “new” potential rejection markers (C-peptide; CRP/Amylase/Lipase combined parameter) will be explored.

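### Section 2.6 correlates the C-peptide/(glucose x creatinine) ratio with glucose and creatinine, its own terms, so those two correlations cannot be interpreted (minor, exploratory)

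*Protocol*

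**What the plan says.** Protocol section 2.6 (non-immunological rejection markers) lists several blood markers, C-peptide alone and a composite among them: "C-peptide and C-peptide/Glucose/Creatinine-ratio (C-peptide : Glucose x Creatinine"). The sentence introducing the list states that the analyses will be "correlated to rejection, functional parameters (glucose levels/need for insulin (P) and creatinine (K)) and graft survival". It covers the whole list and does not exempt the ratio. Sampling is frequent: "By daily blood samples during the first 10 days, thereafter 3 times a week until week 10".

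Section 5 gives the cohort size: "60-80 patients will be enrolled in the study". Section 10.3 sets out the statistical methods and does not mention that the ratio shares terms with two of its comparators. Section 10.2 describes the marker work as exploratory: "potential rejection markers (C-peptide; CRP/Amylase/Lipase combined parameter) will be explored". That sentence names C-peptide but not the ratio.

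**The concern.** A ratio correlated with a quantity in its own denominator is mathematically coupled to it. When glucose is high the ratio is low because it has been divided by glucose, whatever C-peptide is doing. The same holds for creatinine. A reader shown a negative correlation between the ratio and these functional parameters could take it as evidence that the marker tracks graft function, when the division alone can produce it.

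A related point follows from the formula. Because creatinine is a term, the ratio responds to kidney function with the pancreas unchanged. In recipients of a simultaneous pancreas-kidney transplant (SPK), a change in the ratio around a kidney rejection could be read as a pancreas signal.

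At stake is the interpretation of one exploratory marker.

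**Working it through.** The protocol states no correlation, threshold or CV for this analysis, so there is no figure to reproduce. The check is algebra, with a size attached under stated assumptions.

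**Inputs.** From section 2.6: R = C/(G x K), with C = C-peptide, G = glucose, K = creatinine; comparators include G and K. From section 5: 60 to 80 patients. Assumed, because the protocol gives none: CVs of 30-80% (C), 15-50% (G) and 30-80% (K), log-normal values, and C, G and K mutually independent, so that C carries no information on the other two.

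**Formula.** log R = log C - log G - log K. With log-scale variance s^2 = ln(1 + CV^2):

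- corr(log R, log G) = -sG / sqrt(sC^2 + sG^2 + sK^2)
- corr(log R, log K) = -sK / sqrt(sC^2 + sG^2 + sK^2)

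**Example, CVs 50/30/50%.** s^2 = ln 1.25 = 0.2231, ln 1.09 = 0.0862 and 0.2231; the sum is 0.5325 and its root 0.730. Glucose: -0.294/0.730 = -0.40. Creatinine: -0.472/0.730 = -0.65. With equal CVs both are -1/sqrt(3) = -0.58.

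| CV % (C/G/K) | log r, glucose | log r, creatinine | raw r, glucose | raw r, creatinine |
|---|---|---|---|---|
| 50/50/50 | -0.58 | -0.58 | -0.41 | -0.41 |
| 30/30/30 | -0.58 | -0.58 | -0.51 | -0.51 |
| 30/30/50 | -0.47 | -0.75 | -0.40 | -0.58 |
| 50/30/50 | -0.40 | -0.65 | -0.33 | -0.48 |
| 50/30/80 | -0.33 | -0.78 | -0.25 | -0.44 |
| 80/20/30 | -0.25 | -0.37 | -0.21 | -0.30 |
| 70/15/30 | -0.21 | -0.41 | -0.18 | -0.34 |

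Raw-scale values are Pearson correlations from 400,000 simulated triples. Ten combinations were tried; the three not shown lie within the same limits. They do not cover every corner of the assumed ranges. At the corners the log-scale formula gives, for glucose, -0.15 (80/15/80) to -0.75 (30/50/30) and, for creatinine, -0.33 (80/50/30) to -0.91 (30/15/80).

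**Chance of a spurious p < 0.05 (nominal 5%).** This was simulated on the log scale with one value per patient. Over four combinations (50/50/50, 50/30/50, 60/20/30, 80/20/30) it was 50% to about 100% for glucose and 84% to about 100% for creatinine with 60 patients, and 62% and 94% upward with 80. These are not floors: 70/15/30 gives about 37% for glucose with 60 patients, and the corner 80/15/80 about 20%. All are well above 5%.

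**Direction.** Suppose C-peptide truly rises in proportion to glucose, so that log C = log G + noise. Then cov(log R, log G) = sG^2 - sG^2 = 0. A real relation would show as no correlation, while an uninformative C-peptide shows a negative one.

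**Kidney function alone.** If creatinine rises 50% with C and G unchanged, R becomes 1/1.5 = 0.67 of its value, a fall of 33%.

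**After the change.** Under the same assumptions, C-peptide alone correlates with glucose at about 0.00 (-0.00 to 0.01 in simulation).

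**The case against.** The strongest reply is that section 2.6 uses one general sentence for a whole list of markers. It fixes no test, time point or pairing, and a statistical analysis plan could leave the two coupled pairings out. Also, C-peptide alone is already listed, and need for insulin, rejection and graft survival are already comparators, so most of a sound analysis is in place. That limits the consequence. It does not remove the point, because the text as it stands applies glucose and creatinine to the ratio without exception.

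Several stronger readings are tempting and are not supported:

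- *The artefact will be strong and highly significant.* A reader might infer this from the equal-CV case. Every size rests on assumed CVs and independence; the glucose artefact may be only weak to moderate, and raw-scale values are smaller. The significance figures also take one value per patient, whereas sampling is repeated. Coupling is fullest within the same sample and weaker with later values.
- *The rejection comparison is spurious too.* Rejection, need for insulin and graft survival are not terms of the ratio. Counting rejection in either organ belongs to the primary end-point (sections 2.1 and 10.1); section 2.6 does not say it uses that composite. Pancreas and kidney biopsies are taken separately (sections 2.3 and 8), so the organs can be told apart. The figure of about nine SPK in ten in section 1.1 describes the centre's past, not this cohort. What stands is that a kidney-only rejection can move the ratio.
- *The formula is undefined.* Read left to right, the typed expression could mean (C-peptide/glucose) x creatinine, which reverses the sign of the coupling with creatinine. The marker's name largely settles that both terms are in the denominator. Brackets are a tidy-up.
- *A main aim of the study is threatened.* The ratio is not among the objectives in sections 2.1 and 2.2, nor named in section 10.2.

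**Conclusion.** The point holds and is minor. As section 2.6 is written, the ratio is compared with two of its own terms, and those two correlations cannot be interpreted in either direction. The coupling itself is algebra and needs no assumption. Its size does: within the assumed CVs and with mutual independence, the log-scale r is about -0.2 to -0.6 with glucose and -0.4 to -0.8 with creatinine over the combinations tried. Real dependence among the three could shrink, cancel or reverse these values. The 33% fall for a 50% creatinine rise follows from the formula alone. The ratio's other comparisons in section 2.6 are not algebraically coupled, and neither primary end-point nor the sample size is touched.

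**What to change.** In section 2.6:

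- Exclude glucose and creatinine as comparators for the ratio, and correlate C-peptide alone, which is already listed, with those two.
- Test the ratio only against outcomes outside its formula: need for insulin, biopsy-proven rejection with pancreas and kidney-only rejection shown separately, and pancreas graft survival.
- Write the marker as C-peptide / (glucose x creatinine).

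Optionally, fit log C-peptide, log glucose and log creatinine as separate terms, to show whether C-peptide adds anything beyond the other two.

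The cost is a few words in section 2.6 and a slightly different analysis of data and biopsies already planned. No extra samples are needed.

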**2.7 Pancreas transplant monitoring with microdialysis catheters**

- At end of surgery totally three microdialysis catheters will be inserted. The catheters membranes have a 100 kDa pore size, an outer diameter of 0.6 mm and a length of 30 mm. A secure thread is positioned 60 mm from the tip (CMA 65, CMA Microdialysis AB, Stockholm, Sweden).The left abdominal wall will be punctured at three different locations close to each other by a hypodermic needle (Sterican® 14G X 3 1/8 “, B. Braun AG, Melsungen, Germany) through which the microdialysis catheter will be led. After removing the hypodermic needle one microdialysis catheter will be sutured to superfluous connective tissue on the pancreas graft, one will be sutured to the fascia of the right psoas muscle implying that the pancreas graft will be in direct contact with the catheter, and one catheter will be secured close to the duodenoduodenostomy. The catheters will be secured to the skin using a 4.0 thread. Each catheter will be perfused with 6 % hydroxyethyl starch at a rate of 1 µL/minute by microinjection pumps (CMA 107, CMA Microdialysis AB, Stockholm, Sweden), and the samples will be collected in microvials (CMA Microdialysis AB, Stockholm, Sweden)
- Postoperatively the microdialysis samples will be analyzed every second hour at the bedside for glycerol, glucose, lactate, and pyruvate using a microdialysis analyzer (Iscus Flex, CMA Microdialysis AB, Stockholm, Sweden).The lactate to pyruvate ratio will be calculated. Thereafter the samples will be frozen to -20°C and later to -80°C.
- Since this study is the first of its kind and threshold values for detecting e.g. pancreatic graft ischemia, leakages, and rejections have not been established we will not implement e.g. a decision tree in the protocol. However, since not only the physicians responsible for the studies, but also the nurses at ward have substantial experience with the microdialysis method, we expect that deviations from the normal course may lead to prescription of e.g. ultrasound Doppler examinations, and that graft complications thereby may be detected earlier. From a purely scientific point of view one could argue that blinding nurses and physicians for the results would be appropriate. However, we consider this not feasible since the researchers also are responsible for treating the patients and it is important that they have immediate access to the data to reveal e.g. inappropriate sampling.
- The catheters will be left in situ for as long as they are able to sample appropriately, or until the patient is dismissed. The patient may at any time point request removal of the catheters. In our liver studies the patients had well-functioning catheters for a median of 10 days. The catheters are easily pulled out after loosen the skin secure. According to our experience from the liver- and Whipple studies removing the catheters is not associated with any risk or pain. After study completion the samples will be thawed and analyzed en bloc for a wide range of inflammatory mediators including complement factor 5 a and the chemokine CXCL-10, which were specific biomarkers for ischemia and rejection respectively in our previous liver study. These analyses will be performed in [name] lab in the Department of Immunology at our hospital. We will also consider analyzing samples for presence of various micro-RNAs.

**3 STUDY DESIGN**

This is a prospective, single cohort observational study, aimed at using a historical control group as comparison. It will be conducted at our single, national center for organ transplantation in Oslo. All pancreas recipients > 18 years of age, who fulfill the inclusion criteria, will prior to transplantation be asked for inclusion.

#### 4 DURATION OF STUDY

All consecutive PTx recipients during 2-3 years are planned to be enrolled, with an intented number of 60-80 patients. The study will continue until all patients have completed a minimum of 60 months of follow-up or have discontinued participation in the study.

**5 NUMBER OF PATIENTS**

60-80 patients will be enrolled in the study and all will receive the standard quadruple immunosuppressive regime with reduced CS dosing compared with previous cohorts (according to newly changed routine protocol).

####

#### SELECTION OF PATIENTS

- 1. **Inclusion Criteria**Patients will be eligible for study entry if **ALL** of the following criteria are met:
     1. Age ≥18 years
     2. Patients who receive a primary or secondary pancreas transplant, with or without a simultaneous kidney transplant (SPK).
     3. Women who are of childbearing potential must have a negative serum pregnancy test at baseline.
     4. Operability has to be ascertained by preoperativeexamination, performed by nephrologist, transplant surgeon and anesthesiologist.
     5. Signed and dated informed consent form.
  2. Exclusion Criteria

Patients will not be eligible if **ANY** of the following criteria are met:

- - 1. Evidence of systemic infection
    2. Presence of unstable cardiovascular disease.
    3. Malignancy < 5 years prior to entry into the trial (with the exception of adequately treated basal cell or squamous cell carcinomas of the skin).
    4. Panel-reactive antibodies (PRA) > 20% or the presence of donor-specific antigens (DSA).
    5. Any positive test for HBV, HBC or HIV.

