The difficulties encountered with PTx have to some extent been compensated by a very selective attitude towards the donors, but thereby making pancreas grafts a scarce resource. In contrast to other abdominal transplantations such as liver transplantation (LTx) and kidney transplantation (KTx), where repeated biopsies have been used for immunosurveillance, percutaneous biopsies of the pancreas-graft have traditionally been avoided due to a high rate of biopsy-related complications (exocrine leaks/fistulas and bleeding episodes). Thus, fear of acute rejections and lack of adequate rejection markers, have led to a rather intensive immunosuppressive load in PTx recipients.

Solitary pancreas transplantation (SPT) has traditionally been subjected to even higher complication and rejection rates, with inferior graft and patient survival - thus favoring the combined SPK procedure. This has been attributed to an even worse rejection monitoring capability, without a”reporter”/sentinel allograft kidney. No biochemical markers have proven to be effective in rejection surveillance.

Pancreas graft thrombosis is a feared complication in the postoperative course, partly due to the oversized vessels used (coeliac trunk/superior mesenteric artery/portal vein) in conjunction with the low blood flow through an isolated pancreas graft. In the native setting, these vessels also serve the intestines and spleen. Therefore, PTx poses a delicate balance between thrombosis and bleeding complications.

*End stage type 1 diabetes is a devastating chronic disease. PTx offer long term insulin-independency. Efforts should be made to define robust patient selection criteria and offer eligible patients insulin-independency before severe diabetic complications appear.*

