**1.1 The Norwegian experience**

PTx is performed at one single national center in Oslo, and from 1983 to date 300 procedures have been performed (7-11). In recent years, the activity has increased; 22 were performed in 2011 and 28 in 2012. Approximately 9 out 10 PTx’s have been SPK’s, hence only about 10% have been SPTs. In the first period from 1983 through 1987, a duct-occluded segmental pancreas was used for transplantation. From 1988, the whole pancreas graft was used, and the exocrine secretion was drained by anastomosing the duodenal segment to the urinary bladder. This technical solution was chosen partly because it offered some sort of rejection monitoring, by urine amylase counts and cystoscopic pancreas biopsies. However, many patients suffered from chemical cystitis and metabolic acidosis, due to loss of bicarbonate. In 1998 the urinary bladder anastomosis was abandoned, in favor of the more physiological enteric anastomosis, the duodenal segment being connected to the proximal jejunum. However, this solution offered even less options to monitor upcoming rejections, as percutaneous biopsies was mostly avoided due to the previously mentioned hazards.

We have recently examined (12) all PTx’s performed at our hospital during 2006-2010 (n=61; 59 SPK, 2 PTA). Our overall surgical complication rate has decreased from earlier years, but we still suffer a substantial rate of reoperations (about 30% of patients), mainly caused by exocrine leakage, bleeding and vein thrombosis. When comparing the populations with or without reoperation, higher donor age had a significant negative impact. No significant effect of donor age on graft survival was observed. There was a tendency towards better results in female recipients, both regarding surgical complications and graft survival. The rejection rate (altogether about 30%) was significantly higher in the graft loss group, and reoperations were insignificantly associated with graft loss.

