**2.1** **Primary objectives**

- Compare the incidence of *acute rejection episodes* at 6, 12, 36 and 60 months after pancreas transplantation, between our single prospective cohort with lower CS vs a historic, retrospective control group (PTx performed during 2011-2013). The incidence of rejection is defined as the fraction of patients in which rejections episodes (one or more) have been proven by biopsies. For SPK rejection in eitherorgan, pancreas or kidney, counts.
- Compare the incidence of *surgical complications*, involving reoperations and reinterventions, between the prospective study group and retrospective control group.

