**10.1** **Strategy regarding 0-hypothesis**

Regarding the ‘*Incidence of rejection*’, a non-inferior approach seems reasonable. The most important aspect is to avoid the following (Type 1) error: Not detecting an elevated rejection rate in the single cohort observational study group (SCOS), when there in fact is a difference in favor of the historic, control (HC) group, with high-CS dosing.

One could argue to use a one-sided test/“rejection region”, because it is highly unlikely that the low-immunosuppressive regimen will yield a lower incidence of rejection. However, according to statistical tradition, a two-sided test will be demonstrated.

Thus, the *0-hypothesis* will have to be:

H0: *The SCOS group will have a significantly different rejection rate compared to the HC group* (*SCOS Gr.* ≠ *HC Gr.*)

- Between groups comparison of total biopsy-proven rejection rate; based on scheduled and ‘ad hoc’ biopsies from the duodenal segment, pancreas and kidney.

-- Biopsy-proven rejection in either organ (for SPK) contributes to the rejection incidence.

Regarding the ‘*Rate of surgical complications*’, the most important aspect is to avoid the following (Type 1) error: Demonstrating an elevated complication rate in the HC group, when there in fact is no difference.

Also here, one could argue to use a one-sided test/“rejection region”, because it is no reason to believe that the low-immunosuppressive regimen will yield a higher rate of complications. However, according to custom, a two-sided test will be demonstrated. Thus, a natural *0-hypothesis* will be:

H0: *The SCOS group and the HC group will have similar rates of surgical complications* (*SCOS Gr. = HC Gr.*)

- Between groups comparison of surgical complication rate; defined as the fraction of patients experiencing one or more surgical complications, involving reoperation or reintervention.

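### SPK and solitary pancreas recipients are pooled in an unstratified comparison with a historical group of unstated mix, so a difference in transplant type would confound both primary endpoints

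*Protocol*

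**What the plan says.** Under Selection of Patients, the protocol enrols "Patients who receive a primary or secondary pancreas transplant, with or without a simultaneous kidney transplant (SPK"). Both types enter one cohort.

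Section 2.1 makes the comparator a "historic, retrospective control group (PTx performed during 2011-2013"). Its split between SPK and solitary grafts is not given.

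The rejection endpoint is scored differently by type. Section 2.1 states: "For SPK rejection in eitherorgan, pancreas or kidney, counts". Section 10.1 repeats the rule ("Biopsy-proven rejection in either organ (for SPK) contributes to the rejection incidence") and describes the rate as "based on scheduled and ‘ad hoc’ biopsies from the duodenal segment, pancreas and kidney". Section 2.3 schedules kidney-graft biopsies at 6 weeks and 12 months.

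Section 1 says that solitary transplantation "has traditionally been subjected to even higher complication and rejection rates, with inferior graft and patient survival".

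Section 10.3 names the Fisher exact test for both primary endpoints and mentions no stratification. Its two analysis populations do not separate transplant types, and section 2.5 does not list transplant type among the baseline characteristics to be examined.

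The 30% reference rate in section 10.2 is attributed to the centre's own recent data, which section 1.1 describes as "n=61; 59 SPK, 2 PTA". For the programme as a whole, section 1.1 says: "Approximately 9 out 10 PTx’s have been SPK’s, hence only about 10% have been SPTs".

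**The concern.** The primary comparison is meant to show whether the lower-steroid cohort rejects more, and has fewer surgical complications, than the earlier cohort. By the protocol's own account, transplant type bears on both outcomes. In a randomised trial the mix would balance apart from chance. Here nothing balances it, and the named test takes no account of it.

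If the mix differs between the cohorts, part of the observed difference reflects who was transplanted and not the change in regimen. This could create an apparent excess of rejection. It could also hide a real one, which section 10.1 names as the most important error to avoid.

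**Working it through.** **The plan's own figures.** Section 10.2 uses N = [Pn(1-Pn) + Ps(1-Ps)] × c / (Pn-Ps)².
- Rejection, 0.30 vs 0.40, c = 7.9: (0.21 + 0.24) × 7.9 / 0.01 = 355.5 (printed 355).
- Complications, 0.30 vs 0.20, c = 7.9: (0.21 + 0.16) × 7.9 / 0.01 = 292.3 (printed 292).
- Rejection, 0.30 vs 0.60, c = 5.3: (0.21 + 0.24) × 5.3 / 0.09 = 26.5 (printed 27).
- Complications, 0.30 vs 0.15, c = 5.3: (0.21 + 0.1275) × 5.3 / 0.0225 = 79.5 (printed 80).

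All four reproduce. Pooling the transplant types makes none of them wrong.

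**What the 30% describes.** The source cohort was 59/61 = 96.7% SPK. If 30% is its overall rate, the implied SPK rate is (0.30 × 61 - 2r)/59, where r is the rate in the two PTA patients. That gives 31.0% if neither rejected and 27.6% if both did. The 30% is therefore close to an SPK rate, but the cohort was not SPK only.

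**Effect of a difference in mix.** With a common SPK rate in both cohorts and no effect of regimen:

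shift in pooled rate = (change in solitary share) × (solitary rate - SPK rate).

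From the protocol: SPK rate about 0.30; solitary share 3.3% in 2006-2010 and about 10% over the whole programme. Assumed, because the protocol gives no figure: solitary rejection rate 0.15 to 0.60, and the solitary share in each study cohort.

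| Solitary share, control to prospective | Solitary rate 0.15 | Solitary rate 0.30 | Solitary rate 0.60 |
|---|---|---|---|
| 10% to 20% | 0.10 × (-0.15) = -1.5 points | 0 | 0.10 × 0.30 = +3.0 points |
| 10% to 30% | 0.20 × (-0.15) = -3.0 points | 0 | 0.20 × 0.30 = +6.0 points |

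The sign depends on which mechanism dominates. The additional organ that can trigger an event in SPK argues for a lower rate in solitary grafts; the statement in section 1 argues for a higher one. For surgical complications the formula is the same, the organ-count rule does not apply, and section 1 points to a higher solitary rate. The protocol gives no solitary complication rate either.

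**Consequence for the test.** Exact probability of a two-sided Fisher p ≤ 0.05 with no effect of regimen, assuming equal groups of 60 / 80 (the control size is not stated) and a solitary rate of 0.50:
- same rate in both groups, 0.30 vs 0.30: 3.1% / 3.3%;
- solitary share 10% to 20%, 0.32 vs 0.34: 3.5% / 4.1%;
- solitary share 10% to 30%, 0.32 vs 0.36: 4.9% / 6.1%;
- solitary share 10% to 40%, 0.32 vs 0.38: 7.2% / 9.5%.

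Under these assumptions the error rate passes 5% only from a 30% solitary share with 80 per group, or a 40% share with 60 per group.

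**The case against.** The strongest reply is that no change in mix is documented. Both cohorts come from one national centre, the prospective cohort is consecutive, and solitary grafts are about a tenth of the programme. Section 10.2 also calls the numbers needed for a 10-point difference unrealistic and falls back on a doubling, 0.30 to 0.60. Against 30 points, a shift of 1.5 to 3 points is small. Stratified and subgroup analyses are often left to a statistical analysis plan, which is not shown.

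Most of this stands as a limit on size. It does not remove the point. Section 10.3 names the primary test, so improving it is not a complaint about missing detail. The solitary share has also varied at this centre: 3.3% in 2006-2010 against about 10% overall.

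Four stronger readings are tempting, and the documents do not support them.
- *The 30% rate describes SPK only.* The source cohort included 2 PTA patients.
- *The mix will shift because the centre has adopted the duodeno-duodenostomy.* Section 1.1 reports why some centres developed the technique. It does not say that this centre will perform more solitary transplants, and nothing supports a solitary share as high as 40%.
- *More solitary grafts would push the rejection rate up.* The two mechanisms oppose each other, so the direction is unknown.
- *The section 10.4 check on the first 20 patients is undermined.* Its trigger is a doubled rate. If the control rate is 30%, that means 12 of 20. With rates of 0.30 (SPK) and 0.50 (solitary), the chance of reaching 12 is 0.5% with no solitary recipients, 0.9% with two and 1.4% with four. Standardising the control rate for this check would rest on very few patients: section 1.1 gives 22 + 28 = 50 transplants for 2011-2012, or about 5 solitary at 10%, where one event moves the stratum rate by 20 points.

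**Conclusion.** The point holds as an avoidable confounder in an unrandomised primary comparison. The protocol treats the two transplant types as different for both primary endpoints, leaves the control mix unstated and names an unstratified test.

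The bias arises only if the mix differs between cohorts. For rejection its direction is unknown. For a 10-point change in solitary share it is about -1.5 to +3.0 percentage points, resting on an SPK rate of 0.30 and an assumed solitary rate of 0.15 to 0.60. It becomes material only with a large shift in mix together with a very different solitary rate, and the protocol documents neither. The sample sizes are unaffected. The case for changing the plan rests on how little the correction costs more than on the likely size of the bias.

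**What to change.** Leave inclusion criterion 2 as it is.

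1. In section 10.3, stratify the primary comparison of both endpoints by transplant type (SPK or solitary), with an exact test of Mantel-Haenszel type and a common risk difference with its 95% confidence interval.
2. Report the SPK-only comparison alongside it, and the number of SPK and solitary recipients in each cohort.
3. Add transplant type to the characteristics in section 2.5.
4. Note in section 10.2 that the 30% reference rate comes from a cohort of 59 SPK and 2 PTA.

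No change to section 10.4 is needed on this account.

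The cost is wording. Transplant type has to be known for every patient in both cohorts, because the rejection endpoint cannot be scored without it. The drawback is a small loss of precision from a sparse solitary stratum, which will also be too small to interpret on its own.
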